**Secondary safety endpoints**			
Evaluate the safety of CryoGON	TE-AEs and TE-SAEs	Number of TE-SAE, TE-AE with severity ≥grad 2, and TE-AE grad 1, occurring in ≥4% or more of participants	Procedure → Week 12
Evaluate the duration of numbness in the GON innervation area following CryoGON	Days with GON-sensory deficit	Average number of days with numbness	Procedure → Week 12
Evaluate the safety of Conventional GON block	TE-AEs, TE-SAEs, ADE and SADE (treatment-emergent)	Number of TE-SAE, ADE, SADE, TE-AE with severity ≥grad 2, and TE-AE grad 1 occurring in ≥4% or more of participants	Procedure → week 4

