**Figure 1. f1:**
[figure not shown]
Lateral view of the left side of the head illustrating the trigeminal (red) and occipital (blue) nerves. Together, these nerves provide sensory innervation to the entire head and are functionally coupled within the trigeminocervical complex (TCC). A needle illustration indicates the approximate segment of the greater occipital nerve targeted by conventional GON blocks and by the CryoGON procedure. Bilateral treatment (not shown) is performed for both interventions.

Cryoneurolysis is an established treatment in pain medicine.
^
12
^ By applying cold temperatures to neural structures, it induces reversible Wallerian degeneration (axonotmesis) with subsequent regeneration, resulting in a long-acting but reversible nerve block. Cryoneurolysis has demonstrated efficacy in trigeminal and occipital neuralgia, with reported pain relief lasting several months.
^
13–
16
^ A sham-controlled study in cervicogenic headache, in which the control-arm received GON-block with steroids, did not demonstrate a statistically significant between-group effect. The investigators in this trial used anatomical landmarks and nerve stimulation to guide the cryoprobe, and insufficient targeting could have reduced the efficacy in the cryoneurolysis arm. It is to date no published reports on efficacy or safety in primary headache conditions to our knowledge, but cryoneurolysis towards the GON is currently studied in an open label pilot study in chronic migraine (NCT06554886).

Surgical navigation systems enable accurate percutaneous targeting of deep neural structures using pre-procedural imaging and real-time tracking. Applied to the GON, navigation-guided cryoneurolysis (CryoGON) offers a minimally invasive, office-based procedure with the potential to provide longer-lasting preventive benefit than conventional GON blocks.

This trial is designed to determine whether response to a conventional GON block predicts subsequent response to CryoGON in chronic migraine, thereby assessing the clinical utility of the block as a decision tool. Secondary objectives include evaluation of open-label efficacy, safety, tolerability, and feasibility of the CryoGON procedure. To that end, this trial will inform the design of future studies by assessing the feasibility and rational for conducting a sham-controlled trial.

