
Key exclusion criteria include prior GON-targeted injections within 12 weeks of baseline, inability to differentiate migraine days from other headache types, or coexisting secondary headache disorders (except medication overuse headache). Patients with occipital neuralgia or neuropathy or other pain conditions that may confound evaluation of study outcomes will be excluded. Additional exclusions include unstable preventive medication regimens, prior or current occipital nerve stimulation, frequent opioid or any barbiturate use, significant psychiatric comorbidity or abnormal pain behaviour, relevant medical conditions increasing procedural risk (e.g. bleeding diathesis), and ongoing treatment site infection.

Study outline

The study will comprise four in-clinic visits and a series of structured follow-up contacts, separated by observation periods with prospective daily eDiary data collection (
Figure 2). At visit 1, eligibility will be assessed and written informed consent obtained via an electronic signature in a secure institutional digital platform (the eFORSK platform). Eligible participants will then enter a minimum 28-day baseline period, which serves both as a screening phase and to establish baseline data for endpoint assessments. A diary adherence of at least 90% (≥25 of 28 days) will be required to proceed. At visit 2, participants will be re-screened, and those meeting criteria will receive bilateral conventional greater occipital nerve (GON) blocks followed by a minimum 28-day observation period. A structured telephone call will be conducted one week after the procedure to capture any treatment-emergent adverse events and confirm scheduling for visit 3. At visit 3, eligibility will again be reassessed, including review of contraindications to CryoGON, confirmation of ≥90% diary adherence, and stable prophylactic regimens. Participants meeting criteria will undergo the CryoGON procedure (navigation-guided cryoneurolysis of the GON). Structured telephone follow-ups will be performed at weeks 1, 4, and 8, and a final in-clinic assessment will be conducted at week 12 post-CryoGON.

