PGI-C	Patients’ global impression of change (PGI-C) questionnaire is public domain. PGI-C has undergone a formal translation process to Norwegian according to linguistic validation methodology.
AE	Defined according to MDR (EU 2017/745) Art. 2(57).
SAE	Defined according to MDR (EU 2017/745) Art. 2(58).
Treatment-emergent	Refers to AE that occur during or in a prespecified interval after the intervention (separately tabulated for CryoGON (occurring week 1-12 after procedure) and GON block (occurring week 1-4 after injection).
AE severity	CTCAE v6.0 grade 1-5: **Grade 1** Mild; asymptomatic or mild symptoms; clinical or diagnostic observations only; intervention not indicated. **Grade 2** Moderate; minimal, local or noninvasive intervention indicated; limiting age- appropriate instrumental ADL*. **Grade 3** Severe or medically significant but not immediately life-threatening; hospitalization or prolongation of hospitalization indicated; disabling; limiting self care ADL**. **Grade 4** Life-threatening consequences; urgent intervention indicated. **Grade 5** Death related to AE.

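### The numbness endpoint aims at duration but averages days within a 12-week window, so it cannot exceed 84 days and falls short of duration if any numbness persists at week 12

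*Protocol article*

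**What the plan says.** The endpoint is one row of Table 4, under the secondary safety endpoints of the protocol article:

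- Objective: "Evaluate the duration of numbness in the GON innervation area following CryoGON".
- Outcome measure: "Days with GON-sensory deficit".
- Endpoint definition: "Average number of days with numbness".
- Time point: "Procedure → Week 12".

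The study outline in the Methods plans telephone contacts at weeks 1, 4 and 8, and then "a final in-clinic assessment will be conducted at week 12 post-CryoGON". No later contact is described. Table 3 closes the treatment-emergent window for CryoGON at the same point ("occurring week 1-12 after procedure").

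The Introduction, after Figure 1, describes cryoneurolysis as "resulting in a long-acting but reversible nerve block". It cites earlier use in trigeminal and occipital neuralgia "with reported pain relief lasting several months".

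The article gives no expected duration of numbness and no expected share of participants still numb at week 12. Nor does it say how unresolved numbness enters the average.

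**The concern.** Duration is a time-to-event quantity: it runs from the procedure until sensation returns. When observation stops at week 12, the duration of anyone still numb is known only to exceed 84 days. Averaging the days counted so far treats that lower limit as if it were the whole duration. A participant who recovers on day 84 and one who has not recovered then contribute the same number. A participant who leaves earlier while still numb is cut off sooner, which pulls the average in the same direction.

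The reversibility of the deficit is part of the safety argument for the procedure, and this is the only endpoint in Table 4 that addresses how long the deficit lasts. The adverse-event endpoints report counts and grades, not time to resolution. If the average is reported as a duration, and then used in planning the sham-controlled trial that the study is meant to inform, it may suggest a shorter deficit than participants actually had.

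**Working it through.** The protocol states no figure for numbness, so there is nothing to reproduce. The check is what the planned average estimates, and how far that can lie from mean duration.

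**Inputs from the protocol.** The window runs from procedure to week 12, which is 12 × 7 = 84 days. The statistic is a plain average of days. The last contact is at week 12.

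**Assumptions.** Numbness starts at the procedure and is continuous until it resolves, with duration T. No one leaves early. T follows a Weibull distribution with shape k from 1 to 3 and a median from 28 to 168 days. The shape and medians are illustrative and do not come from the protocol.

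**What the average estimates.** With a ceiling of 84 days the average estimates the restricted mean

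E[min(T, 84)] = ∫₀⁸⁴ S(t) dt, where S(t) = P(T > t).

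The shortfall from the mean duration is

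E[T] − E[min(T, 84)] = P(T > 84) × E[T − 84 | T > 84].

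This is never negative. It is zero only if all numbness has resolved by week 12.

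**Without a distribution.** If 30% are unresolved and stay numb for a further 28 to 84 days on average, the shortfall is 0.30 × 28 = 8.4 to 0.30 × 84 = 25.2 days. If 50% are unresolved it is 0.50 × 28 = 14 to 0.50 × 84 = 42 days. If none are unresolved it is 0.

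**With Weibull durations.** Scale λ = median / (ln 2)^(1/k), S(t) = exp[−(t/λ)^k], mean = λ Γ(1 + 1/k). For example, with k = 1 and a median of 56 days:

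- λ = 56 / 0.693 = 80.8, so the true mean is 80.8 days.
- P(T > 84) = exp(−84/80.8) = 0.354.
- Restricted mean = 80.8 × (1 − 0.354) = 52.2 days.
- Shortfall = 28.6 days, and 28.6 / 80.8 = 35%.

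All cases (shortfalls come from unrounded values):

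| Median (days) | k | Still numb at day 84 | True mean | Average to day 84 | Shortfall, days (%) |
|---|---|---|---|---|---|
| 28 | 1 | 12.5% | 40.4 | 35.3 | 5.0 (13%) |
| 28 | 2 | 0.2% | 29.8 | 29.8 | 0.0 (0%) |
| 28 | 3 | 0.0% | 28.3 | 28.3 | 0.0 (0%) |
| 56 | 1 | 35.4% | 80.8 | 52.2 | 28.6 (35%) |
| 56 | 2 | 21.0% | 59.6 | 55.0 | 4.6 (8%) |
| 56 | 3 | 9.6% | 56.5 | 55.6 | 0.9 (2%) |
| 84 | 1 | 50.0% | 121.2 | 60.6 | 60.6 (50%) |
| 84 | 2 | 50.0% | 89.4 | 68.0 | 21.4 (24%) |
| 84 | 3 | 50.0% | 84.8 | 71.9 | 12.8 (15%) |
| 168 | 1 | 70.7% | 242.4 | 71.0 | 171.4 (71%) |
| 168 | 2 | 84.1% | 178.8 | 79.4 | 99.4 (56%) |
| 168 | 3 | 91.7% | 169.5 | 82.2 | 87.3 (51%) |

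Two things follow. First, the size depends heavily on the assumed shape and median, and runs from nothing to more than two thirds of the true mean. Second, the average responds weakly where durations are long. With k = 1, going from a 56-day to a 168-day median multiplies the true mean by 242.4 / 80.8 = 3.0, but the planned average by only 71.0 / 52.2 = 1.4. The share still numb at day 84 doubles over the same step (35.4% to 70.7%) and is observed directly.

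**The case against.** The strongest reply is that the row is coherent as it stands. The outcome measure is days with a deficit and the window is declared, so the average is a valid restricted mean; it is low only against an unrestricted mean that the protocol never names. This largely stands. What remains is that the row's stated objective is duration, the statistic is not labelled as restricted, and nothing beside it shows how many participants are unresolved.

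A second reply is that handling incomplete observations belongs in the SAP. That would be fair if the protocol had left the statistic open. It fixes both the average and the window, so the mismatch with the objective is in the protocol itself.

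Several stronger readings are tempting, and the documents do not support them:

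- A reader might infer that the protocol expects many participants to be numb at week 12. The phrase "with reported pain relief lasting several months" is about pain relief in neuralgias, not numbness. The only duration attached to numbness is the threshold of more than 72 hours for technical success. Describing the block as long-acting makes persistence to week 12 plausible, no more.
- A reader might conclude that duration will be understated by a third or more. That takes an exponential shape and medians of 56 days or longer. The exponential gives the largest shortfall of the shapes examined, and its constant chance of recovery from day 0 sits poorly with the degeneration and regrowth the Introduction describes.
- A reader might say that lasting deficits would be hidden. Hypoaesthesia, anaesthesia and related terms are listed in Table 2 as anticipated device effects, and device effects are counted and graded to week 12 as the primary safety endpoint. Deficits are therefore recorded; what is missing is their time to resolution.
- The protocol has no rule setting unresolved numbness to 84 days. The ceiling follows from averaging days in a window that closes then.

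**Conclusion.** The concern holds in a limited form. As fixed in Table 4, the endpoint measures mean numb days within 12 weeks and does not answer its stated objective of duration. The 84-day ceiling and the direction of any error are certain. The size is not, because it depends on how many participants are still numb at week 12 and for how much longer, and the protocol gives neither. Under the assumed Weibull shapes the shortfall is negligible to modest for medians of about four weeks (0–13%), anywhere from 2% to 50% for medians of 8 to 12 weeks, and more than half for a median of 24 weeks (51–71%). If all numbness resolves by week 12 and no one leaves while still numb, there is no shortfall.

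This is a minor to moderate point on a descriptive secondary safety endpoint in a single-arm exploratory study. The primary analysis, the responder analyses and the sample size do not depend on it.

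**What to change.** Amend the Table 4 row, and carry the same wording into the SAP:

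1. Make the proportion still numb at week 12, with a 95% CI, the main figure. With the target of 70 participants and a proportion of 50%, the half-width is about 1.96 × √(0.5 × 0.5 / 70) = 0.117, or 12 percentage points, which is informative enough for a descriptive safety result.
2. Add a curve of time to resolution, censored at last contact: Kaplan-Meier if resolution dates are recorded, interval-censored if resolution is known only to fall between the contacts at weeks 1, 4, 8 and 12. Report the median only if it is reached. If more than half are still numb at week 12 it will not be, and the proportion then carries the result.
3. If a mean is kept, call it the restricted mean over 84 days and take it as the area under that curve, so that early leavers are not counted as recovered.
4. State that the data support no conclusion on reversibility after week 12. No analysis can supply that from follow-up that ends there.

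The cost is a change of wording. It uses the contacts already planned and alters neither the visits nor the sample size. Making it before the study starts also avoids a later departure from a published Stage 1 endpoint.

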**Tolerability endpoints**			
Evaluate CryoGON procedural discomfort	NRS 0–10 score	Average maximum procedural discomfort during CryoGON procedure, recorded on an NRS (0-10) immediately post-procedure.	Procedure day
Evaluate willingness to repeat CryoGON-procedure	Willingness to repeat at week 12	Proportion answering 'yes' to willingness to repeat CryoGON considering benefits and adverse effects.	Week 12
**Primary feasibility endpoint**			
Determine the technical success	Technical success is a composite outcome(i) surgeon-confirmed completion of planned lesion at intended target with no device deficiency; (ii) participant-reported numbness >72 hours in the expected GON dermatome (bilateral) after 1 week.	Proportion of treated sides meeting both criteria	Procedure day; week 1 phone call
**Secondary feasibility endpoints**			
Evaluate the number of device deficiencies	Device deficiencies	Incidence of device deficiencies affecting the planned procedure (classified by type); per-procedure proportion with ≥1 deficiency.	Procedure day
Evaluate the diary adherence	Number of days of scheduled eDiary days with valid entries	Percentage of scheduled eDiary days with valid entries per period 28 day period; threshold ≥90% considered acceptable.	Week 1-4 post-cGON; Weeks 1–4, 5–8, 9–12 post-CryoGON
Evaluate procedure time	Procedure time in minutes from procedure initiation until completion	The average procedure time.	Procedure day
**Open label efficacy endpoints**			
Evaluate change in headache frequency	Moderate–severe headache days	Change from baseline across weeks 1–4, 5–8, and 9–12 after CryoGON.	Baseline; weeks 1–4; 5–8; 9–12
Evaluate the number of Responders applying different responder thresholds.	≥30%, ≥50%, ≥75%, 100% responder rates	Proportions meeting thresholds (primary reporting window: weeks 9–12).	Weeks 9–12 (also 1–4, 5–8)
Evaluate change in self-reported migraine days	Migraine days (self-reported)	Change from baseline to weeks 9–12 after CryoGON.	Baseline; weeks 1–4; 5–8; 9–12
Evaluate change in acute medication use	Acute medication days	Change per 28-day period across weeks 1–4, 5–8, and 9–12.	Baseline; weeks 1–4; 5–8; 9–12
Evaluate change in Quality of life	MSQ v2.1 (total & domains)	Change in MSQ from baseline to week 12.	Baseline; week 12

GON = Greater occipital nerve, cGON = Convetional GON block, CryoGON = Cryoneurolysis of the GON, AE = Adverse event, SAE = Serious AE, TE = Treatment emergent, ADE = Adverse device effect, SADE = serious ADE, PPV = Positive predictive value, NPV = Negative predictive value, NRS = Numerical rating scale, CTCAE = Common Terminology Criteria for Adverse Events.

### Endpoints related to prediction

To address the primary objective, the primary endpoint is the change in moderate–severe headache days from baseline to weeks 9–12 after CryoGON, analysed as a continuous outcome. The primary analysis estimates the association between change after the GON block (weeks 1–4; primary predictor) and change after CryoGON (weeks 9–12).

While the primary endpoint aims to evaluate whether there is an association between degree of response to conventional GON block and CryoGON treatment, this does not necessarily translate to clinical utility. A statistically significant correlation may indicate that patients who benefit more from the GON block also benefit more from CryoGON, but may not justify the use of GON block response as a binary decision-making
tool.

To that end, we will estimate the predictive capability of GON block response in determining which participants will respond to CryoGON. In this analysis we will identify clinical responders, defined as a ≥30% reduction in moderate–severe headache days from baseline, in both weeks 1-4 after GON block and weeks 9–12 after CryoGON. The proportion of CryoGON responders will be compared between those who did and did not respond to GON block, estimated with a risk ratio and 95% confidence interval (CI). Additionally, the sensitivity, specificity and predictive values of response/non-response to GON block will be estimated to identify the usefulness of this treatment as a diagnostic test for response to CryoGON. These measures will also be presented with 95% CI. The 30% responder threshold is selected as it is reported to translate to a clinical meaningful change in chronic migraine.
^
29
^ Two additional analyses with different responder thresholds definitions are also prespecified, namely (i) 50% responder threshold and (ii) a patient-reported impression of change threshold, based on improvement on PGI-C collected at day 1 and after four weeks following cGON and at the end of study participation following CryoGON.

### Endpoints related to the open-label clinical performance of the CryoGON procedure

Open-label efficacy endpoints

The open-label efficacy of CryoGON will be evaluated based on patient-reported prospective headache diary outcomes and quality of life and patient global impression questionnaires. The migraine day endpoint variable definition is operationalized as any day with headache of minimum 4 hours duration that the participant self-identifies as a migraine, or any headache day that is successfully treated with the use of triptans and/or gepants. Patients unable to distinguish a migraine day from other headache semiologies are ineligible according to study criteria. As such, the ability of participant to identify a migraine day is part of the review at the time of inclusion and ensures that the endpoint is operationalized in a manner that adheres to the HIS’ guideline.
^
17
^ Change in quality of life will be measured with the MSQ v2.1 questionnaire at baseline and week 12. Patient global impression of change will be collected at week 8 and week 12.

Open label safety, tolerability, and feasibility endpoints

Safety will be assessed separately for CryoGON (weeks 1-12 following the CryoGON procedure) and conventional GON block (weeks 1-4 following conventional GON injection) as treatment-emergent adverse events (TEAEs) and treatment emergent serious adverse events (TESAEs), adverse device effects (ADEs) and serious ADE (SADEs). Treatment-emergent refers to all AEs events at or following initiation of the conventional GON (week 1-4) or CryoGON procedure (week 1-12), respectively. All AEs will be coded according to the Medical dictionary for regulatory activities (MedDRA) and grouped and summarised using the lowest level term (LLTs).

Severity assessment will apply the standardized grading criteria from the Common Terminology Criteria for Adverse Events (CTCAE) version 6. Casualty assessment will follow the definition of the Medical Device Coordination Group,
^
30
^ and all TEAE will be categorized as not related or possible, probable or casual related to conventional GON in week 1-4 post-procedure and the CryoGON-procedure in week 1-12 post-procedure. An adverse device effects (ADE) is defined according to ISO 14155:2020 as any adverse event related to the use of an investigational device. This is operationalised for this study as any AE that is assessed to have possible, probable or causal relationship to the CryoGON procedure.

Tolerability will primarily be evaluated by intra-procedural discomfort (NRS 0–10) and additionally, the willingness of the participant to repeat the CryoGON procedure. At week 12, or earlier in the event of participant withdrawal, participants will be explicitly asked to consider the balance of perceived benefits and drawbacks of CryoGON and respond with ‘yes’, ‘no’, or ‘unsure’ regarding willingness to undergo the procedure again. The primary feasibility endpoint will be technical success rate. Technical success is defined as a composite of (i) surgeon-confirmed completion of the planned cryo-lesion at the intended target without device deficiency, and (ii) participant-reported numbness persisting >72 hours in the GON peripheral innervation area as reported by the participant on a telephone call after one week. The second criterium is included with the intention to distinguish prolonged sensory change consistent with cryoneurolysis from transient anaesthesia due to local anaesthetic used during the procedure. Other feasibility endpoints are number of device deficiencies, CryoGON procedure duration and diary adherence across study periods.

Adequate diary adherence is essential for the valid estimation of headache day–based endpoints, particularly responder rates. Therefore, diary adherence is included as an operational feasibility endpoint to enable evaluation of the robustness of the data underpinning both the primary endpoint and the open-label efficacy analyses.

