**TEAE related to the area of administration of the CryoGON-procedure **	
Administration site infection	10066214
Administration site erythema	10074796
Administration site pain	10058049
Administration site swelling	10075107
Administration site pruritus	10075106
Administration site hyperpigmentation	10079246
Administration site hypopigmentation	10079247
Administration site bruise	10075094
Administration site haematoma	10075100
Administration site erosion	10075931
Administration site indentation	10079277
Administration site haemorrhage	10075101
**TEAE related to postprocedural disturbed occipital nerve function (i.e. not restricted to site of administration but the nerve sensory distribution area)**	
Neuropathic pain	10054095
Paraesthesia	10033775
Dysaesthesia	10013886
Hyperaesthesia	10020568
Allodynia	10053552
Hypoaesthesia	10020937
Anaesthesia	10002091

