AE relationship assessment	The following categories from the MDCG 2020-10/1 Rev 1 will be used: **Not related:** Relationship to the CryoGON procedures can be excluded when: - the event has no temporal relationship with the procedure; - the serious adverse event does not follow a known response pattern to procedure and is biologically implausible; - the event involves a body-site or an organ that cannot be affected by the device or procedure; - the adverse event can be attributed to another cause (e.g. an underlying or concurrent illness/clinical condition, an effect of another device, drug, treatment or other risk factors. **Possible:** The relationship with the CryoGON procedures, is weak but cannot be ruled out completely. Alternative causes are also possible (e.g. an underlying or concurrent illness/clinical condition or/and an effect of another device, drug or treatment). **Probable:** The relationship with the CryoGON procedure seems relevant and/or the event cannot be reasonably explained by another cause. **Causal relationship:** the adverse event is associated with the CryoGON-procedure beyond reasonable doubt when: - the event is a known side effect of the any element of the procedure, including cryoneurolysis, or of similar devices and procedures; - the event has a temporal relationship with the procedures; - the event involves a body-site or organ that the procedure is applied to or the procedure have an effect on; - the adverse event follows a known response pattern to cryoneurolysis, - other possible causes (e.g. an underlying or concurrent illness/clinical condition or/and an effect of another device, drug or treatment) have been adequately ruled out; - harm to the subject is due to error in use Cases where relatedness cannot be assessed, or no information has been obtained will be classified as possible.
ADE	Any TEAE with possible, probable or causal relationship to the procedure.
SADE	Any TESAE with possible, probable or causal relationship to the procedure.
Procedural pain (tolerability)	NRS 0–10 discomfort during CryoGON; recorded immediately post-procedure.
Willingness to repeat (tolerability)	Participant-reported willingness to repeat CryoGON (yes/no/unsure) considering experienced benefits and drawbacks.

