**Primary safety endpoint**			
Evaluate the safety of CryoGON	ADEs and SADEs (device-related, treatment-emergent) number and severity	Number of SADEs Number of ADEs and proportion for each ADE with different CTCAE grad (1-5)	Procedure → Week 12

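### Safety is summarised by MedDRA lowest level term and event count, so related harms are fragmented and participants harmed cannot be recovered; the 4% cut affects only the secondary grade 1 rows

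*Protocol article*

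**What the plan says.** The protocol article fixes the safety summary in these places.

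- **Summary level.** Under Open label safety, tolerability, and feasibility endpoints, all AEs are coded in MedDRA and "grouped and summarised using the lowest level term (LLTs".
- **Primary safety endpoint (Table 4).** "Number of SADEs Number of ADEs and proportion for each ADE with different CTCAE grad (1-5". There is no frequency cut. Table 3 defines an ADE as "Any TEAE with possible, probable or causal relationship to the procedure", and events whose relatedness cannot be assessed go into the possible category.
- **Secondary safety endpoint, CryoGON (Table 4).** "Number of TE-SAE, TE-AE with severity ≥grad 2, and TE-AE grad 1, occurring in ≥4% or more of participants".
- **Secondary safety endpoint, conventional block (Table 4).** "Number of TE-SAE, ADE, SADE, TE-AE with severity ≥grad 2, and TE-AE grad 1 occurring in ≥4% or more of participants".
- **Anticipated effects (Table 2).** There are 19 lowest level terms under two headings: 12 for the administration site and 7 under "TEAE related to postprocedural disturbed occipital nerve function". No endpoint sums over either heading.

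All treatment-emergent events are registered in the eCRF (Data collection), so the question is how they are summarised, not whether they are captured.

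**The concern.** The lowest level term is, as its name says, the finest level of the coding dictionary. Table 2 shows what that does here: disturbed occipital nerve function becomes 7 lines, and bruise, haematoma and haemorrhage at the site become 3. A reader of the final report will want to know how many participants had any sensory disturbance, and how many had any local reaction. The endpoint as defined gives counts per fine term and a grade split, and neither answers that. The Introduction and Discussion say these data are to inform a sham-controlled trial, whose planning needs a risk per participant.

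A frequency cut applied to split terms is a further weakness. The Safety section describes the reported events after occipital cryoneurolysis as mostly minor and transient, so the treatment of grade 1 events matters.

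**Working it through.** The plan states no figure on this point to reproduce. Inputs: N = 70 (Sample size), the 4% cut (Table 4), and 7 and 12 terms (Table 2). The event rates and the spread over terms below are assumptions, because the article gives none.

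**1. From terms back to participants.** Suppose the report shows 2 events in each of the 7 nerve-function terms, 14 in all.
- If the 2 in each term are different participants, the number with any such event lies between 2 (the same two people in every term; 2/70 = 2.9%) and 14 (all different; 14/70 = 20.0%).
- If they are only events, the lower end falls to 1 participant (1/70 = 1.4%).

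The same table therefore fits a risk anywhere from 1.4% to 20.0%.

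**2. The cut in participants.** 0.04 × 70 = 2.8, so a term is listed from 3 participants (4.3%), and a term with 2 (2.9%) is not. With one term per participant, up to 4 × 2 = 8 (11.4%) can be unlisted over 4 terms, and 7 × 2 = 14 (20.0%) over 7. Recruitment continues until the technical success set reaches target (Sensitivity analyses), so treated N may exceed 70. From N = 76 the cut is 4, since 0.04 × 76 = 3.04.

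**3. Where the cut applies.**

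| Event | Reported in | Cut |
|---|---|---|
| CryoGON, at least possibly related, any grade | Primary endpoint | None |
| CryoGON, not related, serious or grade 2 and above | Secondary row | None on the natural reading |
| CryoGON, not related, grade 1 | Secondary row | 4% |
| Block, related, grade 1 | Block row, as ADE if that term covers the block | Unclear |
| Block, not related, grade 1 | Block row | 4% |

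Two wording problems sit behind this table. The CryoGON row has a comma before the 4% phrase and the block row has none, so the scope of the cut is open in the CryoGON row. The safety text has events categorised for relation to the block in weeks 1–4, but then operationalises ADE by relation to the CryoGON procedure, and the relationship categories in Table 3 are also written for CryoGON.

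**4. Chance that nothing is listed in a filtered row.** For one grouped line with total rate p, this is P(X ≤ 2) with X ~ Binomial(70, p). At p = 0.10:

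0.9^70 + 70 × 0.1 × 0.9^69 + 2415 × 0.01 × 0.9^68 = 0.0006 + 0.0049 + 0.0187 = 0.024.

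For k terms with rate p/k each and one term per participant, it is the multinomial probability that every count is at most 2 (simulated, 200,000 draws):

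| Assumed total rate | Grouped | 4 terms | 7 terms |
|---|---|---|---|
| 5% | 31% | 79% | 91% |
| 10% | 2.4% | 30% | 55% |
| 15% | 0.1% | 6% | 21% |
| 20% | about 0% | under 1% | 5% |

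An even spread favours non-listing. If half of a 10% rate fell in one term, that term alone would miss the cut with probability P(Binomial(70, 0.05) ≤ 2) = 0.31. The chance that nothing is listed would then be at most 31%, however many other terms there were.

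**The case against.** A reader might infer that a common known harm of CryoGON can drop out of the safety report because its terms each fall under 4%. The document does not support that. The primary safety endpoint reports ADEs of grades 1 to 5 with no cut, and an unassessable event defaults to possible and so counts as an ADE. A Table 2 reaction after CryoGON would ordinarily be judged at least possibly related, so it appears, in pieces. The block row also names ADEs outside the cut. Numbness, the most expected sensory effect, has its own secondary endpoint in days and is part of technical success. These points stand, and the probabilities above do not describe related CryoGON events.

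It can also be said that the proportion for each ADE might be meant per participant, and that participant-level tables and intervals are ordinary SAP content. In part this stands: the denominator is not stated, and a SAP is still to be finalised. But the summary level and the form of the endpoint are fixed in the article, and even proportions of participants per term cannot be summed to a group, as step 1 shows.

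Finally, nothing in the article shows that preferred terms would merge any of the 7 nerve-function terms. That also stands. The calculation supports grouping by the Table 2 headings; the preferred-term summary is an addition without a computed gain.

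**Conclusion.** The point holds as a minor weakness in how safety is summarised. Related CryoGON harms are reported in full but fragmented over up to 7 and 12 terms, and the primary safety endpoint gives no number of participants harmed, overall or for either harm group. This part rests on the text alone and needs no assumed rate.

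The 4% cut is a smaller matter. It affects grade 1 CryoGON events judged not related, grade 1 block events judged not related, and possibly block-related ones. It still has some weight: in an uncontrolled open-label study the all-cause row is the one that does not depend on individual causality judgements. At N = 70 and an assumed 10% total rate spread evenly, with one term per participant, nothing is listed with probability about 30% (4 terms) or 55% (7 terms), against 2.4% when grouped. The 4 and 7 are illustrations, since the article does not say how many terms unrelated or block events would occupy. Serious and grade 2 or higher events are untouched on the natural reading.

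**What to change.** In Table 4, the safety text and the SAP:

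- Keep the lowest level term for coding. Summarise also by preferred term and by the two groups already headed in Table 2, counting each participant once per group.
- Apply the 4% rule at group level as well as to single terms.
- State that the 4% applies to grade 1 events only, and that for the conventional block an ADE means an event related to the block.
- For the primary safety endpoint, report the number of participants with at least one ADE and with at least one SADE, by worst grade, with exact 95% CIs, beside the event counts.

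The cost is wording and slightly longer safety tables. All treatment-emergent events are already recorded and coded, so no new data are needed.
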